### Adverse event reporting and harms {22}

In our study, an adverse event will be defined as medical occurrence in a subject with regard to the possibility of a causal relationship. Adverse events will be collected after the subject has provided consent and enrolled in the study. If a subject experiences an adverse event after the informed consent document is signed (entry) but the subject has not started to receive study intervention, the event will be reported as not related to study drug. All adverse events occurring after entry into the study and until hospital discharge will be recorded. An adverse event that meets the criteria for a serious adverse event (SAE) between study enrollment and hospital discharge will be reported to the Gyeongsang National University Hospital IRB [Institutional Review Board] as an SAE. A serious adverse event for this study is any untoward medical occurrence that is believed by the investigators to be causally related to study drug and results in any of the following: life-threatening condition (that is, immediate risk of death), severe or permanent disability, prolonged hospitalization, or a significant hazard as determined by the Data Safety Monitoring team. Serious adverse events occurring after a subject is discontinued from the study will not be reported unless the investigators feels that the event may have been caused by the study drug or a protocol procedure. Investigators will determine relatedness of an event to study drug based on a temporal relationship to the study drug, as well as whether the event is unexpected or unexplained given the subject’s clinical course, previous medical conditions, and concomitant medications.

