## Trial design {8}

The trial is designed as a randomized, open labeled, multicenter, two-arm with 1:1 allocation clinical trial in South Korea. This study compares the effect of nafamostat mesylate injection with standard treatment on 42 patients with COVID-19 pneumonia in the intervention group versus 42 patients with COVID-19 pneumonia with standard treatment only in the control group.

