### Intervention description {11a}

Eligible patients will be randomized in equal proportions between standard treatment with nafamostat mesylate and standard treatment only.

Experimental group: nafamostat mesylate plus symptomatic treatment and lopinavir/ritonavir, hydroxychloroquine, antibiotics, non-invasive and invasive ventilation, renal replacement therapy (e.g., CRRT, HD), and ECMO as needed

*Nafamostat injection
Dosage: the researcher administers a dose of 0.1 to 0.2 mg/kg/h (2.4 to 4.8 mg/kg/day), taking into account the severity and underlying disease of the clinical trial patient.Method of administration: nafamostat injection is mixed with 1000 ml of 5% DW infusion, followed by continuous infusion over 24 h.Duration of administration: the researcher administers for 10–14 days considering the severity and underlying disease of the clinical trial patient.

Control group: symptomatic treatment and lopinavir/ritonavir, hydroxychloroquine, antibiotics, non-invasive and invasive ventilation, renal replacement therapy (e.g., CRRT, HD), and ECMO as needed

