## Data collection and management

### Plans for assessment and collection of outcomes {18a}

Data on demographic information, underlying disease, initial symptoms, diagnosis date, coronavirus Ct value, and laboratory and radiological findings is collected by the clinician. The clinician evaluates the seven-category ordinal scale of clinical status on admission, NEWS score and clinical course complications at hospitalization, treatment progress and clinical results, and side effects by drugs. Medical history is collected within 1 year before screening. In the case of single malignant tumors, medical history within 5 years before screening is collected. Information about underlying disease such as diabetes, hypertension, liver cirrhosis, chronic kidney disease without hemodialysis, end-stage renal disease, chronic heart failure, and lung diseases is collected regardless of period. At each visit, the National Cancer Institute Adverse Events Standard Terminology (NCI CTCAE) version 5.0 should be documented and recorded. The collection period for these reactions is from the start of treatment in the test or control group to day 28.

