#### Participants withdrawal

The patient has the right to voluntarily discontinue participation in the trial for any reason at any time, and the investigator also has the right to discontinue the patient’s participation in the trial at any time.

Reasons for discontinuing participation in a clinical trial may include, but are not limited to:
Withdrawal of consent from patientsTermination of testing or closing of testing institutionsNon-compliance of patients defined as non-compliance with the clinical trial plan requirements according to the decisions of the tester or clientOccurrence of serious adverse events

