### Composition of the data monitoring committee, its role and reporting structure {21a}

The Data Monitoring Committee (DMC) has not been established. Although DMC is strongly recommended in other clinical studies with significant safety concerns in which double-blind treatment is assigned, this trial is a phase 2 clinical study with confirmed drug safety and is an open label trial, not a double-blinded study. In the pandemic caused by SARS-COV-2, an effective treatment was not established, and the study was conducted in consideration of the exceptional situation in which a therapeutic agent is urgently needed.

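### The SAE definition requires causation by study drug and does not list death, so SAEs cannot be compared between arms; the adverse-event window is also stated inconsistently.

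*Protocol article*

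**What the plan says.** Section {22} of the protocol article makes causality part of the definition. An SAE is "any untoward medical occurrence that is believed by the investigators to be causally related to study drug" that results in "life-threatening condition (that is, immediate risk of death), severe or permanent disability, prolonged hospitalization, or a significant hazard", the last of these being decided by a Data Safety Monitoring team. Death does not appear in the list. The investigators judge relatedness themselves, partly on whether the event is unexplained by the patient's clinical course. The trial is open label ({17a}), so they know the allocation.

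The arms differ only in nafamostat. The comparator is described as "Control group: symptomatic treatment and lopinavir/ritonavir, hydroxychloroquine, antibiotics, non-invasive and invasive ventilation", continuing with organ support as needed, and the design section gives its size: "42 patients with COVID-19 pneumonia with standard treatment only in the control group". The safety outcomes under {12} list SAEs without restriction to one arm.

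On timing, {22} says: "All adverse events occurring after entry into the study and until hospital discharge will be recorded". The data collection section {18a} says: "The collection period for these reactions is from the start of treatment in the test or control group to day 28".

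On oversight, {21a} says: "The Data Monitoring Committee (DMC) has not been established".

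**The concern.** In a randomised comparison, seriousness and causality are separate attributes. Seriousness is a property of the event and can be counted the same way in both arms. Causality is an opinion about one of the two treatments, and here it is formed by people who know the allocation. When that opinion is an entry condition for the SAE count, the count in the arm without the drug is fixed before the trial starts. The safety outcome then no longer estimates a difference between randomised groups.

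The distortion can run either way. A drug effect that looks like worsening COVID-19 pneumonia can be put down to the disease and left out of the SAE count. Conversely, background events attributed to nafamostat are set against an empty control arm and can look like an excess. External reporting narrows as well: the IRB is the recipient of SAE reports named in {22}, and it would see only drug-attributed events in a trial with no data monitoring committee.

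The window is a second, separate problem. A period that ends at discharge is tied to an outcome, because live discharge is part of the primary endpoint and hospital stay is a secondary one.

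**Working it through.** **1. Can a control patient have an SAE?** An SAE in {22} needs two things together: (a) an investigator believes study drug caused the event, and (b) a listed consequence follows. Under {11a}, controls receive no nafamostat. If study drug means nafamostat, (a) is never met in controls, so their SAE count is 0 out of 42 whatever happens to them. Clause (a) alone gives this result. The omission of death from (b) is a separate defect and plays no part in it.

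**2. Is the section consistent with itself?** No. It says SAEs arising after a patient is discontinued go unreported unless thought to be caused by the drug or a protocol procedure. That exception only makes sense if unrelated SAEs can exist, and the definition rules them out.

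**3. Size (illustration).** The plan gives no SAE rate, so there is no figure to reproduce. Assumptions not in the documents: true SAE rate p, the same in both arms; share q of nafamostat-arm events attributed to the drug; at most one event per patient. With n = 42 per arm, the expected control events are n·p, the control events recorded are 0, and the expected nafamostat events recorded are n·p·q.

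With the control count fixed at 0, the two-sided Fisher p-value for r events against 0 is 2·C(42,r)/C(84,r):
- r = 5: 2 × 850,668 / 30,872,016 = 0.055
- r = 6: 2 × 5,245,786 / 406,481,544 = 0.026

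Six recorded nafamostat SAEs are therefore enough for p < 0.05. The chance of reaching six with no true difference is P[Bin(42, p·q) ≥ 6]:

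| p | q | True control events | Control recorded | Nafamostat recorded | Chance of a spurious excess |
|---|---|---|---|---|---|
| 10% | 25% | 4.2 | 0 | 1.1 | 0.1% |
| 20% | 25% | 8.4 | 0 | 2.1 | 1.7% |
| 20% | 50% | 8.4 | 0 | 4.2 | 24% |
| 20% | 100% | 8.4 | 0 | 8.4 | 87% |
| 30% | 100% | 12.6 | 0 | 12.6 | 99.5% |

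Section {20a} names Pearson's chi-square test for categorical variables. Without continuity correction, 4 against 0 already gives 84 × (4 × 42)² / (42 × 42 × 4 × 80) = 4.2, p = 0.040, so Fisher's test is the more cautious illustration.

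At the low-attribution end the error is mainly the opposite one: with p = 20% and q = 25%, about 2 of 8.4 nafamostat-arm events are counted.

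**4. The window, side by side.**

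| Section | Start | End |
|---|---|---|
| Adverse event reporting and harms {22} | Entry, after consent | Hospital discharge |
| Plans for assessment and collection of outcomes {18a} | Start of treatment, either arm | Day 28 |
| Participant timeline {13} | D1 | D28 |
| Provisions for post-trial care {30} | – | Checks continue after discharge |
| Safety outcomes {12} | During treatment | During treatment |

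Neither the start nor the end agrees across these sections. As an example, a patient discharged on day 10 (an assumed day) has about 10 days of recording under {22} and 28 under {18a}.

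**The case against.** **Harm is still visible elsewhere.** A reader might infer that deaths and deteriorations blamed on COVID-19 vanish from the trial. They do not. The secondary outcomes collect day-28 mortality with date and cause, and new oxygen, high-flow or non-invasive ventilation, and ventilator or ECMO use, all regardless of attribution; death is also the worst category of the ordinal scale. This objection stands. It limits the loss to the SAE comparison and SAE reporting.

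**Ordinary adverse events are not affected in the same way.** The adverse-event sentence in {22} mentions a possible causal relationship, and it is tempting to say it shares the fault. But the section records all adverse events and keeps pre-treatment events while labelling them unrelated, and {18a} covers both arms. The wording is unclear, but it does not make relatedness a condition.

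**Study drug is not defined.** True. The structural zero depends on its meaning nafamostat. That is the natural reading, because controls receive no investigational product.

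**The window conflict may be one stray sentence.** Sections {13}, {18a} and {30} all support follow-up past discharge. That makes the repair easy, but the sections still disagree. A reader might infer that the arms will have unequal observation time. The documents give no discharge data by arm, so this is a risk if the discharge cut-off is applied, not an established difference.

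**A monitoring team need not be a data monitoring committee.** Agreed. The absence of a committee does not contradict the reference to a team. The team is simply not identified in the article.

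**The full protocol may read differently.** The amendment history says version 3.0 revised the adverse-event definition, and version 3.1 is current but not shown. The finding is therefore about the article's wording. That wording states a definition; it is not detail left out for brevity.

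**Conclusion.** The concern holds for the SAE definition and for the window. As written, and taking study drug to mean nafamostat, the control arm's SAE count is zero by construction, so a listed safety outcome cannot be compared between arms and the IRB sees only drug-attributed events. The size of the distortion depends on rates the documents do not give. Over assumed true rates of 10% to 30% and attribution shares of 25% to 100%, 4.2 to 12.6 control SAEs would go unrecorded, and the chance of a spurious significant excess on nafamostat by Fisher's test runs from 0.1% to 99.5%. The omission of death as a named criterion is an additional fault.

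What is lost is the SAE comparison and SAE reporting, not all sight of harm. The window statements conflict at both ends, and a cut-off at discharge would make safety observation depend on an outcome that treatment may affect.

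**What to change.** 1. Define an SAE by seriousness alone, identically in both arms, and name death as a criterion.
2. Record relatedness to study drug as a separate item for SAEs, as {22} already has investigators assess it for events generally, and define study drug.
3. Compare all-cause SAEs between arms; drug-related SAEs can be described separately.
4. Reconcile {12}, {13}, {18a}, {22} and {30} to one recording window for adverse events and SAEs, the same in both arms. Randomisation to day 28 is one option that the planned visits and post-discharge contact already support.
5. State who judges whether an event is a significant hazard, and bring the post-discontinuation clause into line with the new definition.

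The cost is changes to protocol and case report form wording, plus some extra SAE forms for disease-related events. No new visits are needed for a day-28 window.

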### Frequency and plans for auditing trial conduct {23}

Auditing is considered both overall and for each recruiting center when participants are enrolled. Audits can be done by exploring the trial dataset or performing site visits by C&R research which is a research assist company with independent to investigators. The CRA will verify the events and adverse reactions that occur in all the follow-up visits and the rest of the variables described in the protocol. The monitoring plan is designed to include at least one initiation and three monitoring visits per year.

### Plans for communicating important protocol amendments to relevant parties (e.g., trial participants, ethical committees) {25}

In April 2020, version 2.0, which is initial version of the trial protocol, was submitted to the Ministry of Food and Drug Safety in Korea (MFDS). MFDS approval was granted on April 17 2020. In May 2020, an amendment (version 3.0) was submitted to the MFDS. Protocol changes in this amendment included the following: the contents of patients without standard treatment (e.g., emergency) were revised by referring to the definition of vulnerable subjects in the clinical trial management criteria, addition of serious adverse events (including LFT abnormalities) to the discontinuation criteria, NEWS (National Early Warning Score) added in clinical data collection, revision of the definition of adverse events and actions to be taken in the event of an adverse reaction, and addition of information regarding the storage institution and disposal method of the consent form for human materials. MFDS approved version 3.0 on May 28, 2020. In June 2020, a minor amendment (version 3.1) was submitted to the MFDS. Protocol changes in this amendment included the following: change schedule in the confirmation of virological endpoints through SARS-CoV-2 quantitative RT-PCR. MFDS approved version 3.1 on June 11, 2020. Patient recruitment commenced in April 2020, and the last patient will be recruited to the trial in April 2021. The last visit of the last patient is anticipated to occur in April 2021.

### Dissemination plans {31a}

There are plans for investigators and sponsor to communicate trial results to participants and public via publication of article.

## Discussion

There is lack of proven therapeutics for COVID-19 patients yet. Although the replication pathways of SARS-CoV-2 are still uncertain, replication of SARS coronavirus is mediated by cell surface and endosomal pathways using a protease, the type II transmembrane protease [9, 10]. Nafamostat mesilate shows an anti-viral effect by an inhibition serine protease, which is required for the host membrane fusion of viral envelope protein. In vitro experiments showed that the drug is effective in MERS-CoV, influenza virus, and 2019-nCoV [3–5, 11].

There are studies that have shown that cytokines are elevated in COVID-19 patients [12, 13]. Nafamostat mesilate has anti-inflammatory effect by inhibition of the complement pathway and inhibition of cytokine production [8].

According to our knowledge, this study is the first randomized clinical trial in the world to evaluate the effect of nafamostat mesilate on the COVID-19 pneumonia. Our study contributes to the establishment of therapeutic strategy by evaluating the therapeutic effect and safety of nafamostat mesilate.

## Trial status

The current protocol version is 3.1, 11 June 2020. The study started on 17 April 2020. The first patient enrolled on 7 July 2020. An approximate date on which recruitment will be completed will be 24 April 2021.
